## Abstract

**Background:**

One Australian loses a limb every 3 h as a result of infected diabetic foot ulcers (DFU). This common condition accounts for substantial morbidity and mortality for affected individuals and heavy economic costs for the health sector and the community. There is an urgent need to test interventions that improve wound healing time, prevent amputations and recurrent ulceration in patients presenting with DFU whilst improving quality of life and reducing health care costs.

**Methods:**

One hundred and fifty eligible participants will be randomised to receive an autologous skin cell suspension, also termed ‘spray-on’ skin (ReCell®) or standard care interventions for their DFU. The primary outcome is complete wound healing at 6 months, but participants will be followed up for a total of 12 months to enable secondary outcomes including total overall costs, ulcer free days at 12 months and quality of life to be assessed.

**Discussion:**

Outpatient costs for dressings, home nursing visits and outpatient appointments are key cost drivers for DFU. If spray-on skin is effective, large cost savings to WA Health will be realised immediately through a shortened time to healing, and through a higher proportion of patients achieving complete healing. Shortened healing times may enable participants to return to work earlier. Any economic benefits are likely to be amplified across Australia and other similar demographic settings where aging populations with increased diabetes rates are considered major future challenges.

**Trial registration:**

Australian New Zealand Clinical Trials Registry ACTRN12618000511235. Registered on 9 April 2018.

## Background

One Australian loses a limb every 3 h as a direct consequence of diabetes related foot disease, usually due to an infected diabetic foot ulcer (DFU) [1, 2]. That amounts to around 8000 lower extremity amputations (LEA) undertaken in Australia each year [3, 4]. In Western Australia (WA) alone, more than 200 major (above the ankle) LEA are performed annually and recurrent minor (below the ankle) amputations in patients with Type 2 diabetes (T2DM) are increasing by about 3.5% per annum [5]. There has been a 30% increase in diabetes-related amputations, largely related to increasing diabetes prevalence [6] in Australia over the past decade and 8% of diabetes-related deaths are attributable to foot complications [1, 2, 7]. These poor outcomes have persisted despite increasing awareness of the medical, economic and social burden of diabetic foot complications [8]. The economic costs and mortality rates exceed that of many common cancers; the 5-year mortality rate of patients with diabetic foot infections is ~ 50% [9–12]. The estimated economic burden in Australia may exceed $1.5 billion, with DFU accounting for 33% of diabetes related costs [13]. Poor outcomes associated with DFU are disproportionately high in the Australian Indigenous population [14]. A recently published systematic review has found that Aboriginal and Torres Strait Islander Australians are 3–6 times more likely to experience a diabetes related foot complication than non-Aboriginal Australians [15]. Therefore there is an urgent need to test interventions to improve healing time, reduce recurrent ulceration and the incidence of LEA in patients with DFU whilst optimising function and quality of life.

In addition to in-patient services required when the DFU becomes limb or life threatening, most of the morbidity and economic burden of DFU is carried by public sector outpatient services. Wound healing time is a key cost driver and influences the overall cost-benefit analysis for any DFU intervention [16]. It is estimated that the mean healing time for a DFU managed without amputation is 6 months, rising to 12 months if an amputation is required [17, 18]. The outpatient component of management accounts for 71% of the total costs associated with DFU and suggests that reductions in the time to healing are likely to have major benefits for direct costs, particularly related to home nursing visits, dressings and outpatient appointments.

### Rationale

We hypothesise that the use of ‘spray-on’ autologous skin grafting (ReCell®; Avita Medical) in DFU will decrease healing time and thereby reduce overall cost of treatment. Autologous ‘spray on’ skin aids epithelial regeneration and has been used successfully in the treatment of scars and burns and other ulcers [19], particularly when traditional split skin grafting is not feasible. Although it has shown some early promise in a small case series of 4 ft ulcers [20] and for other chronic ulcers [19], no randomised trial of this product has been completed or is currently planned. The aim of this study is to assess the potential benefit of spray-on skin as a superior, and cost-effective, management strategy for DFU.

### Hypotheses

Spray-on autologous skin grafting improves wound healing time in patients with DFU compared with standard careSpray-on autologous skin grafting is cost-effective when compared with standard care

## Study design

This study is a prospective, randomised, open label trial powered for superiority. Local and international data informed sample size calculations indicating that, at present, 45% of patients with DFU will achieve complete healing at 6 months [17, 18, 21]. We estimate that 136 (with continuity correction) patients are required to have 80% chance of detecting, at the 5% level of significance, an increase in the primary outcome measure from 45% in the control group to 70% in the spray-on skin group [19]. To account for drop-outs, we will aim to recruit 150 participants in total.

### Study population

The study population will be screened from patients attending the Fiona Stanley (FSH) or Royal Perth Hospital (RPH) inpatient or outpatient multidisciplinary foot units during the recruitment period. The primary ulcer requiring treatment will be considered the index ulcer for enrolment. The site of the index ulcer will be defined at enrolment and categorised as either being fore-, mid- or hindfoot. During the lead-in phase, the wound bed preparation will be standardised prior to randomisation. Recruitment will occur over an 18-month period and participants followed for 12 months.

### Randomisation

Randomisation will take place 2 weeks (+/− 6 days) from the last significant debridement or minor amputation to allow the surgical wound site to demonstrate early healing. Randomisation into treatment (ReCell®) or control (standard care) is performed by randomisation program (REDCap) and researchers are blinded to the randomisation algorithm that will include variable block sizes that are randomly 2, 4 or 8.

### Inclusion criteria

i)Age ≥ 18 yearsii)Diabetes (type 1 or 2) defined according to international consensus guidelinesiii)Admission to FSH or RPH, or visit to outpatients departments with a DFU requiring local debridement or minor amputationiv)Ulcer area > 6 cm^2^v)The ulcer location, contour, shape and wound base is deemed to be suitable for administration of spray on skinvi)No further debridement or amputation is anticipatedvii)Wound bed is adequately vascularised as determined by the presence of at least one palpable pulse in the affected foot, or at least single vessel run off identified by arterial Doppler ultrasonography, MRI, CT or conventional angiography (including following revascularisation procedures)viii)Competent and willing to provide informed consentix)Able to be followed up by ambulatory care services (Silver Chain) for community nursing

### Exclusion criteria

i)Non-diabetic ulcerii)Wounds deemed unsuitable on the basis of contour, location, vascularity or other factorsiii)Limb threatening ischaemia or sepsis requiring early major amputationiv)Not competent to provide informed consentv)Unlikely to be accessible for follow-up visit over the next 12 months

### Primary outcome

The primary outcome for the trial will be a dichotomous outcome of complete healing of the index ulcer at 6 months as defined by full epithelialisation, after debridement of callus, lasting for at least 2 weeks. Primary outcome arbitration at the interim analysis and at the final analysis will be performed using the database, wound dimension and clinical images assessed by two independent senior clinicians (not investigators) blinded to the intervention. Discordant outcome assessments will be resolved by consensus.

### Secondary outcomes

Secondary outcomes include: i) index ulcer free days at 12 months, ii) time to full epithelialisation of the index ulcer, iii) trajectory of wound healing of the index ulcer (defined as volume and measured using Silhouette™), iv) major adverse events, v) any minor or major lower limb amputation, vi) all-cause mortality, vii) re-ulceration of the index ulcer, viii) the development of any new ulcers ix) total costs of inpatient and outpatient costs (see economic analysis, below), x) readmission to hospital and xi) health-related quality of life (as measured by EQ-5D-5 L) [22].

The definitions for secondary outcomes are consistent with international guidelines [23]. Re-ulceration is defined as healing of index ulcer followed by subsequent ulceration with loss of epithelialisation at the same location. A minor amputation is an amputation below the ankle including toe, metatarsal-phalangeal and midfoot amputations. A major amputation is an amputation above the ankle including below knee and above knee amputations. New onset infection includes infections that have commenced during the preceding 2 weeks, including existing ulcers that have never previously been infected.

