### Follow up measurements

Patients will be followed up at predefined time points. This will coincide with routine outpatient visits ordinarily scheduled at 4, 10, 18, 26, 39 and 52 weeks from randomisation with phone consultations every fortnight to determine total ‘ulcer-free’ days following healing. At each scheduled visit, the wound will be assessed in terms of location (exact; forefoot vs. hind- and mid-foot), depth, dimensions, wound volume and wound area (as measured by Silhouette™ [Aranz Medical]), wound quality (patchy vs. confluent, % epithelialisation), probe to bone test and photography. Both feet will be assessed for new wounds. Blood tests will be (lipids, C-reactive protein, full blood examination and renal and liver function tests) will be performed as clinically indicated, but an HbA_1c_ will be measured at 3, 6 and 12 months to determine the change from recruitment. All patients will receive standard care related to off-loading, ongoing diabetes management and infection management as per the usual management protocol of the multi-disciplinary foot ulcer teams. In addition to baseline, an EQ-5D-5 L [22] will be performed at 26 and 52 week visits to ascertain change in health-related quality of life [24]. The primary outcome will be assessed at the 26-week visit.

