### Adverse events

Although it is expected that the intervention will be safe, adverse events (AE) will be pre-specified and reported to the Data Safety and Monitoring Board (DSMB; see below) in accordance with NHMRC position statement of monitoring and reporting of clinical trials. A DSMB will be established that includes an independent researcher and two independent clinicians including one with experience in clinical trials and the other with managing diabetic foot infections. As this is not a systemic intervention, there will be no stopping rules based on any haematological or biochemical parameters.

A severe adverse event (SAE) form will be reported promptly to the DSMB if any of the following occurs:
Death from any causeMajor limb amputation of the same leg as the index ulcer at any stage up to 12 months from enrolmentMajor infection of the harvest site as defined as the requirement for admission to hospital, surgical debridement or intravenous antibiotics

An AE form will be reported if any of the following occurs:
Readmission for any reason related to infection or deterioration of the index ulcerMinor amputation unrelated to the index ulcer, but on the same foot as the index ulcer (after enrolment)Minor infection of the harvest site as defined by erythema and the requirement for oral antibiotic therapy for thisDelayed healing of the harvest site as defined by persistent need for a dressing on the harvest site at or beyond the 4 week visit

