## Statistical considerations

### Primary and secondary outcomes

All analyses will be conducted according to the intention-to-treat principle. Baseline characteristics will be compared by treatment group. Effects of treatment on the primary study endpoint (complete healing of the index ulcer at 6 months) will be estimated with the use of unadjusted logistic regression with last observation carried forward for those lost to follow-up. All *P*-values will be two-sided and *P*-values less than 0.05 will be considered to indicate statistical significance. Multiple logistic regression will be applied to adjust for prognostic factors such as vascular insufficiency and site of DFU (fore-, mid- or hind foot) which are strongly correlated with the outcome (*r* ≥ 0.3) [25, 26]. Binary secondary outcomes at 12 months will be analysed similarly. For continuous secondary outcomes, change score analysis that determines treatment effect based on the difference between baseline and post treatment score (basic adjustment) will be undertaken. Multiple linear regression adjusting for i) the baseline value of the outcome variable in the model (model 1), and ii) model 1 + adjustment for prognostic baseline factors (model 2) will be undertaken. Data will be analysed using IBM SPSS Statistics 25.

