### Health economic analyses

The main perspective of the analyses will be societal. Direct health care costs including spray on skin and usual care treatment costs, hospital inpatient and outpatient costs, including hospital in the home, out-of-hospital medical services and consumables will be estimated. An incremental cost-effectiveness analysis will be performed in which the net costs and net effectiveness of spray on skin will be compared with those of usual care and expressed as ratios. All analyses and comparisons will be performed on an intention-to-treat basis. Since the time horizon for the primary endpoint (complete healing of the index ulcer) is 6 months, discounting will not be performed. The confidence intervals for the incremental cost-effectiveness ratio will be estimated using the bootstrap approach with 1000 repeated random samples drawn with replacement from the original data. Bootstrap confidence intervals will be constructed with the bias-corrected percentile method. Data will be analysed using IBM SPSS Statistics 25 [IBM Corporation].

Overall costs will be determined by length of hospital stay, number and nature of operating theatre visits, use of pathology and radiology services, length of “hospital in the home” treatment, direct antibiotic costs, consumables associated with wound management (dressings, debridement, human skin replacements, negative pressure wound therapy dressings; ambulatory nursing attendance, orthotic appliances (prostheses, casting, shoes, in-soles). To ascertain data on direct costs for outpatient home care nursing we will extract data from the ambulatory nursing services electronic data collection tool (COMCARE™ [Docobo]). Outpatient visit costs will be derived from Medicare rebates (for multidisciplinary team visits and single specialty attendances at podiatry, infectious diseases or vascular clinics), whilst drug costs will be estimated from listed drug costs from Pharmaceutical Benefits Scheme (PBS) published listing, or in the case of moxifloxacin, piperacillin-tazobactam, ertapenem and other non-PBS drugs, from direct pharmacy costs. All costs will be adjusted on a year-by-year basis according to the medical services component of the Consumer Price Index to a single financial year for comparisons (2018).

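### Index-ulcer infection is a reportable adverse event only on readmission, and the defined term for new-onset infection is attached to no listed outcome

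*Protocol article*

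**What the plan says.** The Secondary outcomes section of the protocol article lists outcomes i to xi and then gives definitions, introduced by "The definitions for secondary outcomes are consistent with international guidelines". Four terms follow: re-ulceration, minor amputation, major amputation and new-onset infection. The last reads "New onset infection includes infections that have commenced during the preceding 2 weeks, including existing ulcers that have never previously been infected".

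The Adverse events section says that "adverse events (AE) will be pre-specified and reported to the Data Safety and Monitoring Board", and then lists what prompts a form:

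- **Severe adverse event form (3 triggers):** death; major amputation of the index leg; serious harvest-site infection (needing admission, surgical debridement or intravenous antibiotics).
- **Adverse event form (4 triggers):** readmission because of infection or worsening of the index ulcer; a minor amputation elsewhere on the index foot; harvest-site infection treated with oral antibiotics; slow harvest-site healing.

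The same section adds: "As this is not a systemic intervention, there will be no stopping rules based on any haematological or biochemical parameters".

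Follow-up visits are "ordinarily scheduled at 4, 10, 18, 26, 39 and 52 weeks from randomisation with phone consultations every fortnight". The wound assessments listed for the visits include dimensions, wound quality, a probe-to-bone test and photographs. Infection is not named among them.

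**The concern.** The cell suspension is applied to the index wound, which then stays under an undisturbed contact dressing for at least five days, while controls continue usual wound care. Management of that wound differs by arm, so infection there is a natural local safety comparison, and one to which both arms can contribute. Harvest-site events can occur only in the spray-on skin arm.

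The article sets no laboratory stopping rules because the treatment is not systemic. Local clinical events are then the main safety signal for the monitoring board, and the trigger list largely decides which of them it sees. If infection treated in clinic or at home prompts no form, a moderate excess in either arm could pass unseen unless it led to readmission, amputation or death, or delayed healing.

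**Working it through.** **1. Definitions against the outcome list (Secondary outcomes)**

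| Defined term | Listed outcome |
|---|---|
| Re-ulceration | vii |
| Minor amputation | v |
| Major amputation | v |
| New-onset infection | none |

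Three of the four terms match an outcome, and none of the 11 outcomes names infection. Outcome iv, major adverse events, is not defined in the article and is not tied to infection. The defined term does not appear again.

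**2. The seven triggers by site (Adverse events)**

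Three concern the harvest site (serious infection, minor infection, slow healing). One names infection of the index ulcer, through readmission. The other three are death and two kinds of amputation.

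**3. The same clinical event at the two sites**

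| Management of the infection | Harvest site | Index ulcer |
|---|---|---|
| Oral antibiotics, not admitted | AE form | no form |
| Intravenous antibiotics or surgical debridement, not admitted | SAE form | no form |
| Admitted | SAE form | AE form, as a readmission |

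An index-ulcer infection that ends in death or major amputation gives an SAE form, but records the death or amputation rather than the infection. Two edges are unclear. The Health economic analyses section costs hospital-in-the-home treatment, and the article does not say whether that counts as readmission. If a participant is still an inpatient at randomisation, an infection during that stay is not a readmission.

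**4. Contacts available to record infection**

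The gaps between visits are 10 − 4 = 6, 18 − 10 = 8, 26 − 18 = 8, 39 − 26 = 13 and 52 − 39 = 13 weeks. A two-week look-back at visits alone would miss most of that time. The fortnightly calls match the two-week window, but their only stated purpose is counting ulcer-free days.

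**5. What a comparison could show**

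The documents give no infection risk, so a 12-month risk p of 10% to 40%, equal in both arms, is assumed. With 150 participants, taken as 75 per arm:

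- Expected first episodes: 150 × 0.10 = 15, to 150 × 0.40 = 60.
- Half-width of the 95% confidence interval for the risk difference: 1.96 × √(2p(1 − p)/75).

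| p | Half-width (percentage points) |
|---|---|
| 0.10 | 9.6 |
| 0.20 | 12.8 |
| 0.30 | 14.7 |
| 0.40 | 15.7 |

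Only a large difference would be visible. The value of the item lies mainly in safety monitoring, not in a formal test.

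**The case against.** The outcome list is introduced as what the outcomes include, so it may not be exhaustive, and a journal article condenses the full protocol. The two-week window in the definition fits the fortnightly calls, which makes a line lost in condensation at least as plausible as an outcome that nobody planned. Major adverse events is undefined and could cover more than the printed triggers. Adverse event reporting is also said to follow a national position statement that is not shown. All of this stands, and it reduces the unattached definition alone to something close to an editorial point.

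Infection is part of the disease under study, and both arms receive infection management under the usual team protocol. A higher threshold for an expected disease event, and a lower one for a new wound created by the trial, is a defensible choice. That stands too: the difference between the sites is not in itself an error.

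Consequential infection is partly captured in both arms through readmission, amputation, mortality and the healing outcomes. What remains is infection of the treated wound managed without readmission, for which the printed list has no trigger. Antibiotic costs are collected ("direct antibiotic costs, consumables associated with wound management"), but as costs and not as events.

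A reader might infer that infection goes unrecorded in this trial, that an infection outcome was dropped, or that the trigger list biases the safety comparison against spray-on skin. The documents support none of these. They show only that the printed outcomes and triggers do not name such infection.

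**Conclusion.** The point holds as a minor one. On the printed text, new-onset infection is defined but attached to no listed outcome, and infection of the index ulcer prompts a form to the monitoring board only on readmission. Infection treated without readmission is neither on the trigger list nor named as a between-arm comparison.

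This rests on reading the trigger list as it is printed, and on hospital-in-the-home care not counting as readmission for those episodes treated that way. The number of episodes affected cannot be derived from the documents: the 15 to 60 above follow from an assumed risk and include episodes that would lead to readmission and be reported anyway. The primary outcome, its analysis and the sample size are untouched.

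**What to change.** - **Trigger:** add to the adverse event list, for both arms, new index-ulcer infection requiring antibiotics, with or without readmission. State whether hospital in the home counts as readmission.
- **Ascertainment:** ask the same question in both arms at the existing visits and fortnightly calls: any new infection of the index ulcer, and any antibiotic start with its indication, since the last contact. Make the calls from randomisation in everyone. If they began only after healing, the arm that heals sooner would be asked more often.
- **Reporting:** give the number and proportion with a first episode by 12 months in each arm, with a confidence interval for the difference, as a safety outcome. If a model is wanted, the plan already provides one: "Binary secondary outcomes at 12 months will be analysed similarly".
- **Definition:** attach the existing definition to this outcome, or delete it if it is left over. If the full protocol already has such an outcome, name it in the list.

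**Cost:** one question per contact, one field for antibiotic indication, and at most about 15 to 60 first-episode forms under the assumed risks, fewer where readmission already prompts one. Community nursing, which is an entry condition ("Able to be followed up by ambulatory care services (Silver Chain) for community nursing"), and the antibiotic cost records can help confirm episodes. The main drawback is that infection and prescribing are judged by clinicians who know the allocation, so some ascertainment bias is possible. Identical questions in both arms limit it but do not remove it.
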